## 8.2 CLINICAL MONITORING

Before the initiation of the study, the monitor will:

- Determine the adequacy of the facilities
- Discuss with the Investigator and study personnel their responsibilities with regard to CSP adherence, local regulations, and the duties of monitor
- At an initiation meeting, the monitor will comply with the ICH-GCP Guidelines (ICH-GCP 8.3.20) and document that the study procedures were reviewed with the Investigator and the Investigator’s staff
- During the study, a monitor will pay visits to the investigational site in order to:
  - provide information and support to the Investigator
  - confirm that facilities remain acceptable
  - confirm that the investigational team is adhering to the CSP
  - confirm that data are being accurately recorded in the e-CRFs
  - ensure that accountability checks for the IMP are being performed
  - conduct source data verification, which will require direct access to all original records for each subject (e.g. medical records)

The monitor will be available (by phone, fax and e-mail) between visits whenever the Investigator or other study personnel at the investigational site needs information, advice or help.

All documentation and correspondence pertaining to the study (raw data, letters etc.) should be kept in accordance with ICH-GCP.

## 8.3 AUDITS AND INSPECTIONS

The purpose of an audit or inspection is to systematically and independently examine all study related activities to document that they were conducted, recorded, analyzed and accurately reported according to the CSP and the background regulatory demands.

Audits or inspections may therefore be performed at the study site during or after the study. Visits may thereby be paid by the MPA. These visits may include source data verification and confidentiality documents are therefore created.

The Investigator should contact the monitor immediately if they are contacted by the MPA about an inspection at their study site.

## 8.4 TRAINING OF STUDY PERSONNEL

The Investigator will maintain records of all individuals involved in the study (medical, nursing and other personnel). The Investigator will ensure that appropriate training relevant to the study is given to the personnel involved in the study, and that any new information of relevance to the conduct of the study is forwarded to the persons involved.

## 8.5 CHANGES TO THE STUDY PROTOCOL

Study procedures will not be changed without mutual agreement between the Investigator and Bactavia.

If the clinical study protocol (CSP) needs to be amended, the amendment or a new version of the CSP must be approved by the MPA and the ethical committee before implementation. Approval must also be obtained for the written Patient Information and Informed Consent Form, if applicable.

If an amendment to the CSP substantially alters the study design, or increases the potential risk to the patients, written informed consent must be obtained again for currently enrolled patients and must be provided to additional patients prior to their entry into the study.

## 8.6 PROTOCOL DEVIATIONS

Deviations from the CSP, deemed necessary for an individual subject, will be reported in the e-CRF giving the reason and date. If necessary, the Investigator (or designee) will contact the monitor to inform about the deviation.

## 8.7 STUDY REPORTING

After completion of the study, the Investigator will prepare a clinical study report in co-operation with Bactavia. The Investigator is responsible for submitting the final study report to the MPA.

## 8.8 ARCHIVING

The Investigator shall keep records of the study for 10 years after final signed 12-month Clinical Study Report. This includes any original source documents related to the study, including the subject Identification List with Subject Numbers, full names and the original signed informed consent forms and detailed records of disposition of IMP.

## 8.9 PATIENT CONFIDENTIALITY

The patients have the right to request access to his/her personal data and the right to request rectification of any data that is not correct and/or complete. Investigator or designee personnel whose responsibilities require access to personal data agree to keep the identity of each patient confidential. This agreement is to be substantiated in a separate document.

## 8. 10 Insurance

Participants are covered by “patientskadelagen” and the investigational medicinal product betamethasone is covered by “läkemedelsförsäkringen”.

## 8.11 PUBLICATION

The Investigator is responsible for registering the study in a publicly accessible database before recruitment of the first patient.

The study report (Section 8.7) may form the basis for a manuscript intended for publication in a medical journal. Attempts to publish negative or inconclusive as well as positive results must be made, or otherwise made publicly available.

#

# 9. Ethical considerations

The trial has been registered with the EU’s electronic database of clinical trials (EudraCT), with EudraCT number 2017-002418-30, and sponsor protocol number bactavia1. The trial will be submitted to the Swedish Medical Products Agency (läkemedelsverket) and Regional Ethical Review Board in Stockholm for review. Following approval the study will be started. Patients will be informed of the study verbally and in writing. Details about the trial including risks and benefits will be explained and any questions answered. A copy of the written consent form (appendix C) will then be signed. The use of clindamycin in healthy individuals to study the effect on the intestinal microbiota without access to autologous faecal transplantation was approved by the Stockholm regional ethical board in a recent study ([5](#_ENREF_5)).

**10**. QUALITY CONTROL (QC) AND QUALITY ASSURANCE (QA)

This study will be conducted in compliance with this protocol, standard operating procedures at the study site, the ICH Guideline for GCP and any local regulations.

Audit of the study sites may be conducted to assess and help assure compliance with GCP and applicable regulatory requirements. The study sites may be subject to a QA audit by the sponsor or its representatives, as well as this study may be reviewed by an independent QA department and/or inspected by regulatory authorities. This implies that auditors/inspectors will have the right to inspect the study sites at any time during and/or after completion of the study and will have access to source documents, including patients’ medical records. By participating in this study, the investigator agrees to this requirement.

# 11. Statistics

## 11.1 Power calculation

No power calculation was done for this safety and tolerability study. Twelve patients in each arm are considered sufficient to detect major adverse events whilst avoiding unnecessary exposures.

## 11.2 Duration

Advertising and recruitment will be done during autumn 2017. The study should start around November/December 2017 and run for 6 months. Sequencing and data analysis will take 6 months. A report should be completed by the end of 2018. Within 90 days of the end of the study the “declaration of end of trial notification” document will be sent to the MPA

## 11.3 Data analysis

Final analysis will include a description of included participants, proportions of adverse events and any serious adverse events, the proportion of participants withdrawn or lost to follow up. Categorical variables will be compared between patient groups using the χ^2^ test or Fisher exact test and continuous variables using quantile regression.

For microbiota Shannon indexes for diversity will be calculated in all samples and tested for significance with Wilcoxon rank-sum test. Using the QIIME pipeline, unweighted UniFrac distances are then produced and used for investigation of beta diversity through plotting PCA coordinates

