# 5. Outcomes

## 5.1 Primary endpoint

The safety and tolerability of oral, capsulized, previously frozen, autologous faecal microbiota transplantation up to 21 days after the end of faecal treatment in healthy volunteers.

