# 6. METHODS

## 6.1 Study Design

A double blind placebo controlled phase 1 clinical trial conducted at Danderyds Hospital, Danderyd and Mälarsjukhuset, Eskilstuna both in Sweden.

The double blinded placebo controlled study design has been chosen to enable unbiased assessment of adverse events. The study will be conducted in accordance with the Helsinki declaration on ethical principals for medical research involving human subjects.

Twenty-four volunteers will be included in the study. Following informed consent participants will be requested to donate faeces. Participants will be randomised to treatment group A or B. Treatment will consist of clindamycin 300 mg three times daily for seven days for all. This will be followed by intake of two identical capsules twice daily containing placebo or an autologous faecal mixture for five days. Participants general health and gastrointestinal symptoms will be monitored using questionnaires and stool samples for sequencing of the microbiota will be collected. The study will end when the six month follow up of the last patient ends.

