## 6.5 Randomization

Participants will be concurrently randomly allocated into two arms in a 1:1 fashion. Randomization is to be performed after eligibility has been confirmed and at least 1 hour prior to start of clindamycin treatment.

Patients who fulfil all the inclusion criteria and none of the exclusion criteria are eligible for inclusion into the study and will be randomised into two arms:

- Group A: Clindamycin + Capsules with faeces solution
- Group B: Clindamycin + Placebo Capsules

Randomization is performed centrally.

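### For adverse-event and withdrawal proportions, section 11.3 names only a chi-square or Fisher test as between-arm inference; at 12 per arm a non-significant result would say little about safety

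*Protocol*

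**What the plan says.** Section 5.1 gives the primary endpoint as "The safety and tolerability of oral, capsulized, previously frozen, autologous faecal microbiota transplantation up to 21 days after the end of faecal treatment". It names no single adverse-event variable, margin or decision rule. Section 6.1 explains the design: "The double blinded placebo controlled study design has been chosen to enable unbiased assessment of adverse events".

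On size, section 6.1 says "Twenty-four volunteers will be included in the study", section 6.5 allocates them 1:1, and section 11.1 says "No power calculation was done for this safety and tolerability study", adding: "Twelve patients in each arm are considered sufficient to detect major adverse events whilst avoiding unnecessary exposures".

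On analysis, section 11.3 begins with description, including "proportions of adverse events and any serious adverse events, the proportion of participants withdrawn or lost to follow up". It then gives the comparison: "Categorical variables will be compared between patient groups using the χ^2^ test or Fisher exact test and continuous variables using quantile regression". The section states no significance level, no rule for choosing between chi-square and Fisher, and no risk difference or interval for the adverse-event and withdrawal proportions.

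**The concern.** The trial is randomised and placebo-controlled so that adverse events can be compared between arms. A test of no difference can point to harm when the excess is large. When it is not significant, it does not show how much excess harm remains possible. With 12 per arm, most true excesses of plausible size would give a non-significant result, so the named method usually could not answer the question the control arm was set up for.

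The study is meant as a step towards prophylactic use in patients at risk of *C. difficile* infection (section 2). Its readers will want to know the largest excess risk that the data leave open. Per-arm proportions and a p-value do not tell them.

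The open choice between the two tests adds a second weakness. At this sample size the tests can fall on opposite sides of 5% for the same table.

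**Working it through.** **Inputs from the protocol.** 24 participants (6.1), 1:1 allocation (6.5), 12 per arm (11.1); chi-square or Fisher for categorical variables (11.3). The only figure of the plan that can be reproduced is 2 × 12 = 24, and it agrees. There is no stated power to reproduce.

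**Assumptions, because the protocol gives no values.** Two-sided 5% level; true control risks from 10% to 40%; a doubling as the illustrative effect; no dropout (fewer participants would tend to lower power further).

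**Step 1: which tables are significant.** Let a be the participants with an event in the faecal arm and b those on placebo. All 13 × 13 = 169 pairs (a, b) were enumerated, and the two-sided Fisher p-value and the uncorrected chi-square p-value were computed for each. The smallest a that reaches p ≤ 0.05 is:

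| Placebo events b | 0 | 1 | 2 | 3 | 4 | 5 |
|---|---|---|---|---|---|---|
| Fisher | 5 | 7 | 8 | 9 | 10 | 11 |
| Chi-square | 4 | 6 | 7 | 8 | 9 | 10 |

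For each b from 0 to 5, chi-square needs one event fewer than Fisher.

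**Step 2: the two tests on one table, 4/12 v 0/12.**
- Fisher: 2 × C(12,4)/C(24,4) = 2 × 495/10626 = 0.093.
- Chi-square: 24 × (4×12 − 0×8)² / (12 × 12 × 4 × 20) = 55296/11520 = 4.8 on 1 degree of freedom, p = 0.028.

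**Step 3: miss rate.** Power is the sum, over the significant tables, of Bin(a; 12, p_F) × Bin(b; 12, p_P), where p_F and p_P are the true risks in the faecal and placebo arms. The miss rate is 1 − power.

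| True risk, placebo v faecal | Fisher | Uncorrected chi-square |
|---|---|---|
| 10% v 20% | 98% | 93% |
| 20% v 40% | 91% | 82% |
| 25% v 50% | 86% | 74% |
| 30% v 60% | 79% | 64% |
| 40% v 80% | 61% | 43% |

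The Yates-corrected chi-square gives the same power as Fisher in these scenarios. The miss rate depends strongly on the control risk: at the extreme of 50% v 100% it falls to 19% / 7%.

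**Step 4: what an interval would show, 3/12 v 0/12.** Fisher gives p = 0.22 and chi-square p = 0.064, so neither is significant. The Wilson 95% limits are 0.089 to 0.532 for 3/12 and 0 to 0.242 for 0/12. The Newcombe limits for the difference of 0.25 are:
- lower: 0.25 − √[(0.25 − 0.089)² + (0.242 − 0)²] = 0.25 − 0.291 = −0.041
- upper: 0.25 + √[(0.532 − 0.25)² + 0²] = 0.532

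The same non-significant table is thus compatible with anything from 4 points fewer to 53 points more participants with the event on faecal capsules. Even 0/12 v 0/12 leaves −24 to +24 points by this method.

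**The case against.** A reader might infer that the plan will declare the capsules safe if the test is not significant. The protocol does not support that reading. It sets no such rule, no significance level and no equivalence claim, and it does not designate a primary safety hypothesis test. The sentence on tests is general and follows a descriptive plan that already reports adverse-event, serious adverse-event and withdrawal proportions. Adverse events are also graded individually for seriousness, intensity and causality (section 7.4). All of this stands, and it limits the point to what the named test can tell.

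It is also fair that a phase 1 study in 24 healthy volunteers need not be powered, that section 11.1 says so openly, and that a doubling of risk is not the protocol's own target. The point therefore asks for no more participants. A single headline miss rate would also be wrong, because the result depends on a control risk that the protocol does not give.

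Quantile regression is not part of the problem. It estimates a between-arm difference for continuous variables, and intervals can come from the same model. Power figures for a t-test or rank-sum test on the health scores would not apply, since section 11.3 plans neither for them.

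The strongest remaining objection is that confidence intervals are usually left to a statistical analysis plan, which may exist. That would answer a complaint about missing detail. Here the protocol itself selects the between-arm method for categorical outcomes, and a better one for this purpose is available at no cost in data.

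**Conclusion.** The point holds for adverse-event and withdrawal proportions. The only between-arm inference named for them is a test that, at 12 per arm and an assumed two-sided 5% level, misses a doubled risk in 98% / 93% of trials at a 10% control risk, falling to 61% / 43% at a 40% control risk (Fisher / uncorrected chi-square). The choice between the two tests is left open and can change the result. A non-significant finding would therefore carry little information about safety, whatever wording the report uses. The significance level, control risks and doubling are assumptions; the sample size and the tests are the protocol's. This should be changed, but it does not invalidate the design.

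**What to change.** In section 11.3, make estimation the main between-arm comparison for the safety proportions:

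- For participants with at least one adverse event, each principal symptom listed in section 7.1, IMP-related events, and withdrawal, report the count per arm and the faecal-minus-placebo risk difference with a 95% interval by a small-sample method, such as Newcombe or an exact unconditional interval. Name one method in advance, so that the choice cannot be made after the data are seen.
- Treat any chi-square or Fisher p-value as descriptive, and state that non-significance will not be taken as evidence of safety.
- Keep quantile regression for the health scores and report its between-arm difference with a 95% interval.

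The cost is a few sentences in the protocol and a few lines of analysis code, with no extra data, visits or participants. The downside is that the intervals will be wide, as the 3/12 v 0/12 example shows, so the safety statement will be more modest.

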# Summary

*Clostridium difficile* is an opportunistic pathogen that causes diarrhoea and colitis and is associated with a 2.5 fold increased mortality risk. Infection typically arises following destruction of the intestinal bacterial composition (microbiota) by antibiotic treatment. Patients at risk of *C. difficile* infection can be identified through risk factors such as age and planned antibiotic exposure during e.g. planned medical interventions. *C. difficile* infection is typically treated with antibiotics. However, infection recurs in up to 30% of patients after a first episode and in up to 60% after two or more recurrences. Recurrent infections are most effectively treated by inoculating the diseased gut with bacteria from a donor (faecal microbiota transplantation). Faecal transplantation is typically a prolonged process involving family members, extensive screening and optimally gastroscopy or colonoscopy. Filtered and concentrated stool samples from unrelated donors put into capsules and frozen have recently been shown to be safe and efficacious. This study aims to assess the safety and tolerability of capsules containing autologous microbiota compared to placebo in healthy volunteers after antibiotic exposure. The time to recovery of intestinal microbiota will be determined using the next generation sequencing platform developed by Science for Life Laboratory. The long-term aim is to establish a method whereby patients can leave a stool samples prior to planned antibiotic exposure that can be used prophylactically to reconstitute intestinal microbiota whereby the risk of *C. difficile* infection is minimised and to enable rapid treatment of patients needing a faecal transplant.

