## 5.2 Secondary endpoints

To determine rate at which the composition of intestinal microbiota is normalised through next generation sequencing of stool samples collected for up to six months

To determine the time to normalisation of stool habits

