## 6.10 Monitoring and follow up:

Upon inclusion clinical records form (appendix A) will be completed.

Stool habits and characteristics will be monitored daily from treatment start until day 28 and at 2 and 6 months using the structured questionnaire in appendix B. Questionnaires record stool frequency and consistency, general and gastrointestinal well-being via a standardized health score, rating of gastrointestinal symptoms and medication use. Overall and gastrointestinal-specific health scores will be reported on a scale of 1 to 10, with 1 being the lowest and 10 being “best possible health for you.”

Stool samples for sequencing will be taken at baseline and on days 10, 16 (+3 days if necessary), 28 and at 2 and 6 months.

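### The microbiota endpoint concerns composition, but Section 11.3 tests only diversity, leaves the composition measure as a plot, and does not use each participant's own pre-clindamycin sample as the reference

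*Protocol*

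**What the plan says.** Section 5.2 gives the first secondary endpoint as "To determine rate at which the composition of intestinal microbiota is normalised through next generation sequencing of stool samples collected for up to six months". The Summary words the same aim as a time: "The time to recovery of intestinal microbiota will be determined using the next generation sequencing platform".

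Section 6.10 sets the sampling: "Stool samples for sequencing will be taken at baseline and on days 10, 16 (+3 days if necessary), 28 and at 2 and 6 months". That is six sequencing samples per participant. One precedes clindamycin, one (day 10) falls around the start of the capsules, and four come afterwards.

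Section 11.3 gives two microbiota analyses. The first is "For microbiota Shannon indexes for diversity will be calculated in all samples and tested for significance with Wilcoxon rank-sum test". In the second, "unweighted UniFrac distances are then produced and used for investigation of beta diversity through plotting PCA coordinates". The section does not say which groups or time points the rank-sum test compares. Its general rule for continuous variables, quantile regression between groups, names no baseline term and no within-person term.

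**The concern.** The endpoint and the analysis address different quantities. The endpoint is about composition and its return to a normal state over time. The only tested quantity is a diversity index, and the only quantity that carries composition is drawn and not compared.

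The trial is well placed to do better. The capsules hold the participant's own stool, donated before the antibiotic (Section 6.1 and the footnote to Table 1), so the natural meaning of recovery is return to that person's own earlier flora, and the samples needed to measure it are already scheduled.

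At stake is whether the trial can report anything quantitative on this endpoint. An arm whose diversity recovers with different organisms would look normalised on the tested measure. An arm whose composition came back sooner might show it only by eye on a plot.

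**Working it through.** **No figure to reproduce.** Section 11.1 states that there was no power calculation, and the protocol gives no alpha, effect size or correlation for the microbiota data. The inputs from the protocol are 24 participants allocated 1:1 (12 per arm; Sections 6.1 and 6.5) and six samples each (Section 6.10). Everything else below is assumed: two-sided 5% tests, normal data, and correlations of 0.3, 0.5 and 0.7.

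**Step 1: endpoint against analysis.**

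| Question | Shannon, rank-sum | UniFrac, plot |
|---|---|---|
| Does it measure composition? | No | Yes |
| Is it compared or tested? | Yes | No |
| Is the own pre-clindamycin sample the reference? | No | Not stated |
| Are one person's samples linked? | No (unpaired test) | Not stated |

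Neither column gives a rate, a time, or a distance from the starting state.

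**Step 2: equal Shannon is not equal composition.** With H = -Σ p ln p, take community 1 with four taxa at 0.4, 0.3, 0.2 and 0.1, and community 2 with four different taxa at the same proportions. For both, H = 0.367 + 0.361 + 0.322 + 0.230 = 1.280. They share no taxon, and their Bray-Curtis dissimilarity is 1.0, the maximum.

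**Step 3: what the rank-sum test does under each reading of the text.**

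(a) All six samples per person pooled between arms as if independent. The variance is understated by a factor of about 1 + (6 - 1) × ICC, so the false-positive rate is about 2[1 - Φ(1.96/√(1 + 5 ICC))].

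| ICC | Factor | Formula | Simulation (6,000 runs) |
|---|---|---|---|
| 0.3 | 2.5 | 21-22% | 21% |
| 0.5 | 3.5 | 29% | 29% |
| 0.7 | 4.5 | 36% | 36% |

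Pooling only the four samples from day 16 on gives 15%, 21% and 27%.

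(b) A separate test between arms at each time point. Each test is valid (simulated size 4-5%). The chance of at least one false positive if the tests were independent is 1 - 0.95⁴ = 19% for four tests and 1 - 0.95⁶ = 26% for six. With correlated samples the simulated values are lower: 12-16% for four and 16-23% for six.

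(c) A later sample against baseline within one arm (n = 12). Treating paired data as unpaired is conservative: the false-positive rate is about 2%, 1% and 0.1% at the three correlations. For an assumed fall of 0.8 SD, power is 40%, 41% and 42%, against 52%, 67% and 89% with a signed-rank test.

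**Step 4: what a covariate could gain at one time point.** The difference detectable with 80% power is (1.960 + 0.842) × √(1 - r²) × √(2/12) SD, where r is the correlation with the covariate.

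| r | Detectable difference | Power at 0.8 SD, adjusted |
|---|---|---|
| 0 | 1.14 SD | not simulated |
| 0.3 | 1.09 SD | 46% |
| 0.5 | 0.99 SD | 56% |
| 0.7 | 0.82 SD | 73% |

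The unadjusted rank-sum test has 41-44% power at 0.8 SD in the same simulations.

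**The case against.** Several parts of the defence stand.

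- **The samples are used.** A reader might infer that the plan ignores the baseline, day-10 and repeated samples. It does not: Shannon is calculated in every sample, and UniFrac distances come from the same sequencing. What is missing is the link within a person and the use of an earlier sample as a reference.
- **Inflated error is not established.** A reader might infer that the plan raises the false-positive rate to 21-36%. That needs reading (a), and the text says only that the index is calculated in all samples, not that they are pooled in one test. Reading (b) is valid test by test, and (c) is conservative. The protocol attaches no confirmatory claim to this endpoint, so multiplicity is a lesser matter.
- **The power gain is not known.** The higher figures need correlations of 0.5-0.7, which the protocol does not report, for a day-10 covariate taken soon after clindamycin. At a difference of 1 SD and r = 0.3 the adjusted model has about 67% power, against 65% for a plain t-test. The simulations used normal data, not UniFrac distances. In randomised arms an unadjusted comparison at one time point is inefficient at worst.
- **The endpoint states no comparative hypothesis.** Section 5.2 does not say that autologous capsules restore the flora faster, so the plan cannot be faulted for failing to test that exact claim.
- **The ordination label is minor.** A distance matrix is normally displayed by principal coordinates rather than PCA, but no inference depends on it.
- **The SAP is not shown.** It may define normalisation, the comparisons and the covariates, and the general quantile-regression rule could be stretched to cover distances.

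The last point does not remove the mismatch. Section 11.3 gives the microbiota data their own methods: a test of diversity and a plot. Those written choices do not deliver the endpoint in Section 5.2.

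**Conclusion.** The concern holds as a mismatch between endpoint and analysis. Followed as written, Section 11.3 yields a test of diversity and a picture of composition, with no estimate or test of whether, or how quickly, composition returns to its pre-antibiotic state. This rests on the text and on the Shannon example, not on the simulations.

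The numerical cost cannot be fixed from the documents. It ranges from none (a single valid comparison with a weakly correlated covariate) to a seriously inflated error rate (pooled samples), depending on a reading the text leaves open and on unreported correlations.

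The endpoint is secondary in a 24-person safety study, so the primary safety and tolerability conclusion is unaffected. The change should be made because it is cheap and makes the endpoint answerable.

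**What to change.** Replace the microbiota paragraph of Section 11.3 along these lines:

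- For each post-capsule sample (days 16 and 28, 2 and 6 months), compute the unweighted UniFrac distance to the same participant's pre-clindamycin sample. Table 1 marks faecal samples at both inclusion and day 1, so state which one is the reference.
- Compare these distances between arms in one repeated-measures model with arm, time, arm × time and a participant effect, and with the day-10 distance as covariate. Name one key time point in advance.
- State that the day-10 stool precedes the first capsule. Table 1 places it in the washout column, but day 10 also opens the treatment column, and the covariate is sound only if it is unaffected by the capsules.
- Analyse Shannon the same way, adjusted for its baseline value.
- Keep the ordination as a descriptive display.
- If a time to normalisation is to be reported as well, define the distance that counts as normalised, in the protocol or the SAP, before unblinding. The model describes the course of recovery but does not supply that threshold.

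The cost is a little more analysis work and one extra model term with 24 participants. No sample, visit or participant is added.

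### Unweighted UniFrac is the only named comparison of composition between samples, and because it ignores abundance, a trace of swallowed baseline flora can draw the faecal arm towards baseline on the plot

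*Protocol*

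**What the plan says.** Protocol section 5.2 sets the secondary endpoint: "To determine rate at which the composition of intestinal microbiota is normalised through next generation sequencing of stool samples collected for up to six months". It gives no numerical definition of normalised.

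Section 11.3 names two microbiota measures. The first is within-sample diversity: "For microbiota Shannon indexes for diversity will be calculated in all samples and tested for significance with Wilcoxon rank-sum test". The second is the only comparison between samples: "unweighted UniFrac distances are then produced and used for investigation of beta diversity through plotting PCA coordinates". The protocol names no weighted UniFrac or other abundance-based distance.

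The arms in section 6.5 are "Group A: Clindamycin + Capsules with faeces solution" and "Group B: Clindamycin + Placebo Capsules". Table 1 places the capsule course on days 10-15. Section 6.10 schedules sequencing samples at baseline, on days 10, 16 (with three days' leeway) and 28, and at two and six months. The assay is 16S amplicon sequencing (section 6.11.2).

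**The concern.** Composition means which taxa are present and in what proportions. Unweighted UniFrac sees only the first part: a taxon found in one read counts as much as one holding 30% of the community. Shannon sees proportions but not which taxon holds them, and it makes no comparison with baseline. Neither named measure shows whether a participant's own taxa have returned at something like their former abundance.

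The gap is not neutral between arms. Group A swallows its own pre-antibiotic flora and Group B swallows none. An amplicon assay detects DNA from material passing through the gut as well as from resident bacteria, and the day 16 sample follows directly on the capsule course. A small quantity of swallowed baseline material can therefore restore presence in one arm only. Randomisation and blinding do not remove this, because it is part of the treatment contrast. At stake is how the UniFrac plot is read: faster return to baseline in the faecal arm could be inferred while the dominant flora is equally disturbed in both arms.

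**Working it through.** The protocol gives no figure on this point, so there is nothing to reproduce. The check asks how far a trace of baseline stool moves each measure.

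**Definitions.** Let b be the baseline taxon proportions, d the post-clindamycin proportions, and f = (1 − t)d + tb the same disturbed community with a fraction t of baseline material. Over tree branches of length l:

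- Unweighted UniFrac = (sum of l over branches present in one sample only) / (sum of l over branches present in either).
- Normalised weighted UniFrac = Σ l·|p − q| / Σ l·(p + q), where p and q are the proportions below each branch.
- Share of gap closed = (distance of d to b − distance of f to b) / (distance of d to b − distance between two sequencing draws of b).
- For Shannon, share closed = (H_f − H_d) / (H_b − H_d).

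**Why the two distances part company.** For the weighted distance, b − f = (1 − t)(b − d), so the numerator shrinks by exactly the fraction t. A 1% trace closes about 1% of the gap, whatever the read depth. For the unweighted distance, what matters is whether a lost taxon is seen at all. With N reads, the trace supplies N × t reads. At t = 1% that is 100 reads at N = 10,000, 200 at N = 20,000 and 500 at N = 50,000. Over 200 taxa these average 0.5, 1 and 2.5 reads per taxon, enough to turn many absences into presences.

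**Simulation A.** Assumed inputs, none from the protocol: 200 baseline taxa, log-normal abundances (log SD 1.5), about 60% of taxa lost and the rest distorted (log SD 2), 20,000 reads, 40 replicates, coalescent and star trees. Share of gap closed (coalescent / star):

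| Trace t | Unweighted UniFrac | Weighted UniFrac | Shannon |
| --- | --- | --- | --- |
| 1% | 48% / 38% | 1% / 1% | 3% / 3% |
| 2% | 64% / 52% | 2% / 2% | 5% / 5% |
| 5% | 80% / 69% | 5% / 5% | 11% / 11% |
| 10% | 89% / 82% | 10% / 11% | 22% / 22% |

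Worked line, star tree, t = 5%:

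- Unweighted: (0.66 − 0.22)/(0.66 − 0.02) = 0.44/0.64 = 69%.
- Weighted: (0.79 − 0.75)/(0.79 − 0.04) = 0.04/0.75 = 5%.
- Shannon: (2.47 − 2.25)/(4.21 − 2.25) = 0.22/1.96 = 11%.

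**Simulation B.** 200 taxa, log-normal abundances, about 60% lost, random binary trees, 200 replicates, t = 1%. The shares here ignore the small replicate distance.

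- At 50,000 reads, unweighted distance to baseline falls from 0.39 to 0.14: 0.25/0.39 = 64% from these rounded values (about 63% unrounded). Weighted distance falls from 0.352 to 0.349: 0.003/0.352 = 0.9%.
- At 10,000 reads, unweighted distance falls from 0.40 to 0.28: 0.12/0.40 = 30%.

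**Sensitivity.** With 20-60% of taxa lost and 10,000 reads, a 1% trace closes 20-39% of the unweighted gap. A 0.1% trace closes 4-8% at 10,000 reads and 11-20% at 50,000. A further set of assumed inputs gave 18-65% for a 1% trace and 0-22% for a 0.1% trace.

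**Limiting case.** With abundances permuted among the same taxa, unweighted distance is 0.003, the Shannon difference is 0.0 and weighted distance is 0.33. This is a constructed extreme, not an expected state after clindamycin, but it shows that the two named measures together can miss a changed composition.

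**The case against.** Much can be said for the plan, and most of it stands as a limit on the point.

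- **UniFrac is plotted, not scored.** A reader might infer that the trial will score trace taxa as restored composition and so report a false benefit. The protocol does not support that: it sets no cut-off for normalised and no test on the distances. Shannon has the named test and uses abundances. In simulation A a 1-10% trace closes only 3-22% of its deficit, so most of the disturbance would still show.
- **Carry-over is mainly a day 16 matter.** A reader might infer that the distortion is the same at every sampling day. Capsules end by about day 15. Baseline taxa seen on day 28 or at two and six months more plausibly reflect persistence, which autologous reconstitution is meant to achieve. What remains at those times is that the measure ignores how abundant the returned taxa are.
- **The size is assumed.** Read depth, taxon loss, tree shape and trace fraction are not in the protocol. At a 0.1% trace the effect is small.
- **The metric is legitimate.** Presence and absence suit the loss and return of taxa after antibiotics. Section 11.3 does not call it exclusive, and other distances can be computed from the same reads.
- **Read depth and the PCA label.** A common read depth is detail that a statistical analysis plan would ordinarily hold. PCA in place of principal coordinates is a wording slip. Neither belongs to this point.

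These arguments do not remove the mismatch. The protocol chose a presence-only measure as its sole named comparison of composition, in a trial where one arm swallows the taxa whose presence is counted.

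**Conclusion.** The point holds as a limited, cheap improvement. For the composition endpoint, section 11.3 names only a presence/absence distance, and the second measure does not compare taxa with baseline. A trace of swallowed baseline flora can bring the faecal arm visibly nearer to baseline on the plot while abundances remain disturbed. Under the assumed inputs a 1% trace closes roughly 20-65% of the unweighted gap and about 1% of the weighted gap. The direction was the same in every setting with a 1% trace; the size depends on read depth and taxon loss and fades at a 0.1% trace.

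The documents do not support reading this as a fault that will produce a positive result, or as one that makes every return of baseline taxa an error. The endpoint is secondary, in a 24-person phase 1 study whose primary aim is safety and tolerability. What is affected is what may be concluded about composition from the UniFrac plot. If the statistical analysis plan, which is not at hand, already adds an abundance-based distance and limits the claim accordingly, the point is met.

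**What to change.** In section 11.3, compute abundance-weighted UniFrac beside unweighted UniFrac from the same reads and report both. Add a sentence that no claim of normalised composition, or of a difference between arms in it, will rest on the unweighted distance alone. Fixing this beforehand also avoids choosing the metric after the plots have been seen.

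The cost is one extra distance to compute and report, with no new samples, visits or participants. The weighted distance is less sensitive to rare taxa, which is why the unweighted one should be kept alongside it.
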